## Abstract

**Background:**

Neonatal alloimmune thrombocytopenia (NAIT), caused by maternal antibodies raised against alloantigens carried on foetal platelets, is a very common haematological abnormality in newborns worldwide. However, baseline data on NAIT in China are lacking. Therefore, this study seeks to explore the incidence of alloantibody against the human platelet antigen (HPA) in pregnant women and its associations with NAIT in China.

**Methods:**

A multicentre, prospective cohort study design will be used, and 55,497 pregnant women will be recruited for the first screening of the anti-HPA antibody at 12 to 28 weeks of gestational age. Subjects who are positive in the first screening for the anti-HPA antibody will be included in the exposure group. Re-tests of the antibody titre, antigen-specificity and genotyping of HPA and HLA will be conducted during admission. A ratio of 1:1 paired individuals with the same ethnicity and parity but testing negative for the anti-HPA antibody will be randomly selected to be included in the non-exposure group. NAIT will be diagnosed in the newborns on day one of the birth. The HPA of the neonates in the exposure group will also be genotyped by sequencing. Associations of maternal HLA with the occurrence of the anti-HPA antibody and correlation of the severity of NAIT with the titre of the anti-HPA antibody will be further analysed.

**Discussion:**

The study is expected to provide baseline data on NAIT in China. Besides, we hope to find out a population who expresses particular HLA molecules has significant higher risk of HPA alloimmunization in Chinese individuals. We also hope to find a Chinese-specific cut-off antibody titre for the prediction of the severity of NAIT and to provide a means to evaluate the necessity of antenatal treatment.

**Trial registration:**

ClinicalTrials.gov: NCT02934906 (date registered: 13.10.2016).

## Background

Neonatal alloimmune thrombocytopenia (NAIT) is caused by maternal immunoglobulin G (IgG) antibodies raised against incompatible human platelet alloantigen (HPA) carried on foetal platelets. Foetal platelets are sensitized by anti-HPA IgG and destroyed by the monocyte-phagocyte system [1]. Although many cases are mild, NAIT is one of the most frequent causes of severe thrombocytopenia (platelet count <50 × 10^9^/L) and intracranial haemorrhage (ICH) [2].

The HPA is highly polymorphic. Currently, 35 HPA antigens have been indexed in the Immuno Polymorphism Database (IPD) (http://www.ebi.ac.uk/ipd/hpa/). The antigen type of HPA varies according to ethnicity, which directly causes differences in the incidence and antigen-specificity of anti-HPA antibodies and the morbidity of NAIT. In Caucasian populations, the majority (>75%) of NAIT cases are due to fetomaternal incompatibility of HPA-1a [3]. In contrast, anti-HPA4b and anti-HPA5b are the main causes of NAIT in the Japanese population [4]. The incidence of NAIT is 1 in 1000 in Caucasians [5] and 1.5 in 1000 in Japanese subjects [4].The consequence of NAIT in women with HPA-4b or HPA-5b is less severe than that in Caucasian women with anti-HPA-1a. Generalized purpura and even ICH have been found in HPA-1a-incompatible neonates [2]. In the Japanese population, purpura has been found to develop rarely in HPA-4b-incompatible infants and not to develop in HPA-5b-incompatible infants [4].

It has also been reported that the presence of HPA antibodies is tightly associated with human leukocyte antigen (HLA). Among these antibodies, the most well known is HLA-DRB3*0301, which is strongly associated with alloimmunization to HPA-1a [6, 7]. The immunization rates also correlate linearly with the number of pregnancies. The anti-HPA antibody (mainly against HPA-4b and HPA-5b) has been found in only 0.19% (95% CI: 0.11-0.28%) of women in their first pregnancy and in 1.97% (95%CI: 1.41-2.54%) of women in their fourth or subsequent pregnancies [4].

Few data have been reported regarding the incidence and antigen-specificity of the anti-HPA antibody, the morbidity of NAIT and clinical outcomes among Chinese patients. Therefore, this study seeks to provide these baseline data on NAIT caused by anti-HPA antibodies in pregnant Chinese women.

## Methods/design

This study is a nationwide, prospective, non-interventional, multicentre cohort study. The objectives are listed in Table 1. The survey and data collection will provide baseline data on NAIT in China and help form an appropriate clinical screening procedure.

**Table 1 Tab1:** Study objectives

Primary objectives	
• The positive incidence of the anti-HPA antibody in pregnant Chinese women.	
• The morbidity of NAIT in anti-HPA antibody-positive pregnant women in China.	
Secondary objectives	
• Antigenic specificity of anti-HPA antibodies.	
• Association of the anti-HPA antibody with HLA genotype.	
• The relationship between the titre of the anti-HPA antibody and the clinical symptom severity of NAIT.	

This study is non-interventional. The assignment of subjects to antenatal treatments (such as intravenous immunoglobulin and intrauterine fetal platelet transfusion) or a particular delivery planning is not decided in advance but instead falls within current practice.

Study recruitment started primarily at the sponsor centre at The Second Affiliated Hospital of The Third Military Medical University on 1 November 2016. All other centres initiated consecutive recruitment before the end of January 2017. Recruitment is expected to be completed before December 2018.The goal is to enrol 55,497 women at 12-28 weeks of gestation.

The study subjects will be pregnant Chinese women and their newborns. Inclusion and exclusion criteria are listed in Table 2. Subjects with NAIT in a previous pregnancy or a positive family history of first degree relatives will not be excluded but will be analyzed hierarchically.

**Table 2 Tab2:** Inclusion and exclusion criteria

Inclusion criteria
• Pregnant women 18–50 years of age
• Pregnant women at 12-28 weeks of gestation between 1 January 2017 and 31 December 2018.
• Willingness of the mother to give birth in a participating hospital
• Willingness to participate in the study
Exclusion criteria
• Pregnant women unwilling to participate in the study
• Pregnant women planning to prematurely terminate the pregnancy

### Determination of sample size

For one of the primary objectives, the investigation of the positive incidence of the anti-HPA antibody, we calculated the sample size by using a formula for cross-sectional studies: $$ n={Z}_{\alpha /2}^2p\left(1-p\right)/{\delta}^2 $$. On the basis of an estimated positive rate of the anti-HPA antibody of 0.19% according to a study in Japanese patients [4], an α error of 0.05 and an β error of 0.2, the estimated sample size should be 55,497 to offset a dropout rate of 10%. For the other primary objective, the investigation of the morbidity of NAIT in anti-HPA antibody-positive pregnant women, we calculated the sample size by using a formula for cohort studies: $$ n={\left({Z}_{\alpha}\sqrt{2\overline{p}\overline{q}}+{Z}_{\beta}\sqrt{p_1{q}_1+{p}_0{q}_0}\right)}^2/{\left({p}_1-{p}_0\right)}^2 $$. On the basis of an estimated morbidity of NAIT of 16.7% in the anti-HPA antibody-positive group and 2.5% in the antibody non-exposure group according to the Japanese data [4], an α error of 0.05 and an β error of 0.1, the estimated sample size of anti-HPA antibody-positive subjects should be 98 if a 10% dropout rate is considered. Because the estimated positive incidence of the anti-HPA antibody is 0.19%, the estimated sample size should be 51,578. To ensure that both of these two primary objectives can be addressed in this study, 55,497 pregnant women will be recruited. A sample size review will be performed after the first 10,000 recruitments.

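### The 0.19% antibody rate behind both sample-size totals is a first-pregnancy rate, although enrolment is not limited by pregnancy number; the error is conservative, but the totals and expected positives need restating

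*Protocol article*

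**What the plan says.** In the protocol article, the section Determination of sample size uses one antibody rate for both primary objectives.

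- For antibody incidence, it proceeds "On the basis of an estimated positive rate of the anti-HPA antibody of 0.19% according to a study in Japanese patients [4" and enters that rate into a precision formula. With 10% dropout this gives 55,497 women. The margin δ is not stated.
- For NAIT in antibody-positive women, it needs 98 positives and converts that number into women to screen: "Because the estimated positive incidence of the anti-HPA antibody is 0.19%, the estimated sample size should be 51,578".

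The Background cites the same source but ties the figure to a subgroup. The antibody "has been found in only 0.19% (95% CI: 0.11-0.28%) of women in their first pregnancy", against "1.97% (95%CI: 1.41-2.54%) of women in their fourth or subsequent pregnancies [4". It adds: "The immunization rates also correlate linearly with the number of pregnancies".

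Enrolment is not confined to first pregnancies. Table 2 has no such criterion, and the Methods/design section keeps women who had NAIT in an earlier pregnancy. The section Recruitment and informed consent matches controls on parity, and the section Statistical analysis tests pregnancy number against antibody incidence.

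**The concern.** The plan expects women with varied pregnancy histories and an antibody rate that depends on those histories. It is nevertheless sized as if every woman were in her first pregnancy. By the article's own account, any share of later pregnancies pushes the cohort rate above 0.19%.

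Three planning figures are affected: the recruitment target, the number to screen, and the expected number of positives. The last also sets the workload. Each positive woman brings one matched control. She also brings titration, specificity testing and HPA typing of mother and infant, and HLA typing is done for the mothers in both groups. If the rate is understated, laboratory and follow-up work at 24 hospitals is planned on too small a base, and many more women may be screened than the stated aims require.

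**Working it through.** **Inputs from the article.** p = 0.19%; α = 0.05; 10% dropout; NAIT 16.7% against 2.5% with β = 0.1; 98 positives; rates of 0.19% (first pregnancy) and 1.97% (fourth or later), with a linear rise.

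**1. Reproduce the stated totals.**

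- Incidence: n = 1.96² p(1−p)/δ². With p = 0.0019 and δ = 0.2p = 0.00038, n = 50,451.3, rounded up to 50,452; × 1.1 = 55,497. The unstated margin is therefore consistent with ±20% of p, and dropout was added as × 1.1.
- NAIT: the two-proportion formula with Z = 1.96 and 1.2816 gives 88.4, so 89 per group; × 1.1 = 98. The rate 0.19% does not enter here.
- Screening: 98/0.0019 = 51,578.9; the article gives 51,578.
- Expected positives: 55,497 × 0.0019 = 105.

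Both totals depend directly on 0.19%.

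**2. Rates by pregnancy number (linear interpolation, an assumption).** The step is (1.97 − 0.19)/3 = 0.593 points, giving 0.19%, 0.783%, 1.377% and 1.97% for pregnancies 1, 2, 3 and 4+.

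**3. Overall rate under assumed mixes.** The article gives no mix, so these are illustrations. For example, 80% first and 20% second pregnancies gives 0.8 × 0.19 + 0.2 × 0.783 = 0.309%.

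| Assumed mix 1/2/3/4+ (%) | Overall rate | Positives in 55,497 | N for ±20% relative, × 1.1 | Screened for 98 positives | Positives in first 10,000 |
|---|---|---|---|---|---|
| 100/0/0/0 (as planned) | 0.19% | 105 | 55,497 | 51,578 | 19 |
| 80/20/0/0 | 0.31% | 171 | 34,120 | 31,750 | 31 |
| 70/20/7/3 | 0.45% | 247 | 23,630 | 22,020 | 45 |
| 50/30/13/7 | 0.65% | 359 | 16,230 | 15,150 | 65 |
| 40/35/15/10 | 0.75% | 418 | 13,910 | 13,000 | 75 |

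N is 1.1 × 1.96²(1−p)/(0.04p); screened is 98/p.

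**4. Direction of the error.** With 50,452 evaluable women, the 95% half-width relative to p is 20% at 0.19%, 15.7% at 0.31% and 10.0% at 0.75%. Relative precision improves. The absolute half-width widens from 0.038 to 0.048 and 0.075 percentage points. For the NAIT comparison, positives exceed 98 at every rate in the table.

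**The case against.** The strongest reply is that 0.19% is the lowest rate the article quotes, so planning on it protects both primary objectives. The need for 98 positives is unaffected, and the extra positives help the HLA and titre–severity analyses. At 98 positives and 16.7% there would be only about 16 NAIT cases, so a smaller cohort is not clearly better. The review after 10,000 women would also show the discrepancy. All of this stands, and it rules out treating the point as a threat to validity. It does not make the input correct: the section presents 0.19% as the estimated rate, not as a deliberate lower bound, and it states no rule for the review.

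Three stronger readings are tempting, and the article does not support them.

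- *A planned absolute precision of 0.038 points is missed.* No δ is stated, and the total fits a relative margin, on which precision improves. Holding 0.038 points at a rate of 0.5% would take about 145,600 women, so this reading also conflicts with any claim that N could fall.
- *The article's own figures prove a rate near 0.9%.* The NAIT incidence of "1.5 in 1000 in Japanese subjects [4" divided by 16.7% is 0.90%, whereas 0.19% × 16.7% gives 0.32 per 1000. The division assumes that all NAIT arises in antibody-positive women and that both figures share one case definition. The planned 2.5% in antibody-negative women does not fit the first assumption.
- *The crude rate is the wrong primary result.* The objective is the rate in pregnant Chinese women, which is a legitimate target, and pregnancy number is already analysed.

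**Conclusion.** The point holds as an error of planning input. A first-pregnancy rate is applied to a cohort open to all pregnancies, and 55,497, 51,578 and the implied 105 positives all inherit it. The contradiction lies between two sections of the article and needs no outside source.

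Its size is uncertain. With assumed mixes and linear interpolation, the overall rate is about 0.3% to 0.75%, or 1.6 to 4 times the planning value, and expected positives rise in proportion to about 170 to 420. This also takes the Japanese rates as applicable to Chinese women, as the plan does.

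The consequence is possible over-recruitment and an understated typing and follow-up workload, not loss of power or bias. Severity is moderate.

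**What to change.** In the section Determination of sample size:

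1. Replace 0.19% with an overall rate weighted by pregnancy number. State the assumed mix and a range.
2. State δ and whether it is absolute or relative. The present total matches a relative margin of 0.2p.
3. Restate both totals, the expected positives and the half-width for each rate in the range. If 55,497 is kept to support the secondary objectives, say so and give that as the reason.
4. Specify that the review at 10,000 women re-estimates the overall rate and the resulting N. About 19 positives are expected there at 0.19%, against about 31 to 75 over the assumed range.

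In the section Statistical analysis, report the antibody rate by pregnancy number alongside the overall rate, not in place of it.

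The cost is a reworded section and one short table. On the relative margin no extra women are needed.

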### Recruitment and informed consent

The study is being conducted at 24 Grade-A Tertiary Hospitals in China. Subjects testing positive in the anti-HPA antibody test at 12-28 weeks of gestation will be included in the exposure group. A ratio of 1:1 paired individuals with the same ethnicity and parity but negative in the anti-HPA antibody test will be randomly selected to be included in the non-exposure group. The investigators will inform the participants about all aspects about the trial. The informed consent will include permission to collect blood samples from the mothers and their infants for antibody screening and genotyping of HPA and HLA, gathering data from their medical records and the storage of biological samples for a maximum of 10 years for additional analyses related to the current study. The participants will be informed that trial participation is voluntary and that they are free to withdraw at any time. All the investigators are aware of the guidelines for good clinical practice [8].

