### Study procedure and data collection

All healthy pregnant women receiving regular care at the obstetrical outpatient department of participating hospital will be counselled and asked at 12-28 weeks of gestation to participate in this study. General information will be collected and the anti-HPA antibody evaluation will be conducted after informed consent is received. The test of the antibody titre and antigen-specificity will be conducted at the production admission if the anti-HPA antibody test is positive. Genotyping of HPA will be further completed for anti-HPA antibody-positive mothers and their infants. Genotyping of HLA will be performed for mothers in both the exposure and non-exposure groups. Platelets of their newborns at day one of the birth will be counted, NAIT and ICH will be diagnosed.

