## Discussion

To the best of our knowledge, this will be the first large Chinese cohort study to prospectively investigate the incidence of the anti-HPA antibody in pregnant Chinese women and the morbidity of NAIT in their newborns. Currently, HPA antibodies are not routinely screened for in every pregnant woman, and NAIT is always diagnosed after the birth of the first affected child. Therefore, antenatal treatment can be offered only in the subsequent pregnancies to avoid the recurrence of severe FNAIT [12]. The findings of this study should not only provide baseline data on NAIT in Chinese newborns but also aid in evaluating the necessity of the screening of the anti-HPA antibody in pregnant Chinese women.

A discrepancy between the expected and the actual rates of HPA alloimmunization in pregnancy has previously been observed. For example, in Caucasian women, 2% have the HPA-1b/b genotype, and 98% are married to a man with the HPA-1a gene. However, only 10% of HPA-1a-incompatible pregnancies result in alloimmunization of HPA-1a [13, 14]. One explanation for this discrepancy is that HPA-1a alloimmunization is strongly associated with the HLA-DRB3*01:01 [7, 13, 15]. The HPA-1a alloepitope presented by HLA-DRB3*01:01 has been further identified by using CD4 T cell clones from alloimmunized HPA-1b/b mothers [16]. Except for HLA-DRB3*01:01, HLA-DQ*02:01 has also been reported to be associated with HPA-1a alloimmunization [6], and HLA-DRB1*15:01 has even been found to be inversely linked to FNAIT occurrence [17].The chance of incompatibility with other HPA antigens is greater than that with HPA-1a. However, even fewer cases of FNAIT have been reported to be caused by antibodies against these antigens [1]. Given the large differences in the HLA gene background, little is known about the association of HLA alleles and HPA alloimmunization in Chinese individuals. Our study will also evaluate this key point.

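### The control rule matches on ethnicity and parity but not on hospital, which leaves the secondary HLA–antibody association open to confounding by region

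*Protocol article*

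**What the plan says.** The control rule stands in the Abstract (Methods) and again under Recruitment and informed consent: "A ratio of 1:1 paired individuals with the same ethnicity and parity but negative in the anti-HPA antibody test will be randomly selected". The matching condition in both places is "with the same ethnicity and parity", which names two matching factors. Neither names hospital or region, and neither says from which pool of women the control is drawn.

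The setting is broad. Methods/design states: "This study is a nationwide, prospective, non-interventional, multicentre cohort study". Recruitment and informed consent adds: "The study is being conducted at 24 Grade-A Tertiary Hospitals in China".

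The paired groups carry the HLA objective. Study procedure and data collection says: "Genotyping of HLA will be performed for mothers in both the exposure and non-exposure groups". No HLA typing is described for other women.

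Under Variable and potential confounders, the list covers nationality, maternal history, platelet transfusion history, and maternal and neonatal disease. Centre is not on it. Under Statistical analysis, both thrombocytopenia between groups and maternal HLA genotype against the antibody are tested by chi-square. No stratification, adjustment or use of the pairing is stated for either.

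**The concern.** For the HLA objective the women are selected by antibody status and their genotypes are then compared, so in structure it is a matched case-control study. The controls should show the HLA frequencies of the population that produced the positives. If positives cluster in some hospitals while controls are spread over all of them, and carriage of an allele differs between those places within the same ethnicity, the comparison partly measures region. An allele could then look like a risk marker, or a true marker could be masked.

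The article's Discussion hopes to identify Chinese women at higher risk by their HLA type, so a false signal would bear on a stated aim. The choice is also best made at selection. With about four positives per hospital, adjusting for 24 centres afterwards would be imprecise.

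**Working it through.** **Inputs from the protocol article.** 24 hospitals; 55,497 women; antibody-positive rate 0.19%; "estimated morbidity of NAIT of 16.7% in the anti-HPA antibody-positive group and 2.5% in the antibody non-exposure group"; "an α error of 0.05 and an β error of 0.1"; 98 exposed women after a 10% allowance for dropout; 1:1 controls.

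**The plan's own figure.** With p1 = 0.167, p0 = 0.025, mean 0.096, two-sided Z = 1.96 and Z for 90% power = 1.2816, the stated cohort formula gives

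n = (1.96·√(2·0.096·0.904) + 1.2816·√(0.167·0.833 + 0.025·0.975))² / 0.142² = 88.4, so 89 per group.

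Then 89 × 1.1 = 97.9, so 98, as stated. 98/0.0019 = 51,578.9, against the stated 51,578. The comparison size of 98 per group is reproduced and is used below.

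**Availability of same-hospital controls.**
- Women per hospital, if centres are of equal size: 55,497/24 = 2,312.
- Expected positives: 55,497 × 0.0019 = 105, or 105.4/24 = 4.4 per hospital.
- Negatives per positive: (2,312 − 4.4)/4.4, about 525.

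**HLA illustration (assumed values, since no regional figures are given).** Take two regions with equal numbers screened, no true association within either, and controls drawn from the pooled negatives. Let the antibody rate in region 2 be k times that in region 1, with carriage c1 and c2 of some allele.
- Share of positives from region 2: s = k/(1 + k).
- Carriage among positives: (1 − s)·c1 + s·c2.
- Carriage among controls: (c1 + c2)/2.

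The type I error is for one nominal 5% test with 98 per group.

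| c1, c2 | k | positives v controls | spurious OR | type I error |
|---|---|---|---|---|
| any | 1 | equal | 1.00 | 5% |
| 20%, 30% | 1.5 | 26.0% v 25.0% | 1.05 | 5.3% |
| 20%, 30% | 3 | 27.5% v 25.0% | 1.14 | 6.8% |
| 10%, 30% | 1.5 | 22.0% v 20.0% | 1.13 | 6.4% |
| 10%, 30% | 3 | 25.0% v 20.0% | 1.33 | 13.3% |
| 10%, 30% | 4 | 26.0% v 20.0% | 1.41 | 16.9% |

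Example, last row: s = 4/5 = 0.8; 0.2·0.10 + 0.8·0.30 = 0.26; OR = (0.26/0.74)/(0.20/0.80) = 1.41.

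**Thrombocytopenia illustration (assumed).** Use the same model with no antibody effect and baseline rates of 1% and 4%, which average to the plan's 2.5%.
- k = 1.5: 0.4·1% + 0.6·4% = 2.8%, an excess of 0.3 points.
- k = 3: 0.25·1% + 0.75·4% = 3.25%, an excess of 0.75 points.

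The planned difference is 16.7 − 2.5 = 14.2 points.

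**With same-hospital controls.** Positives and controls then have the same hospital distribution, so the between-hospital bias in this model is zero. The 98, the 1:1 ratio and the assay count do not change.

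**The case against.** The strongest reply is that this is a journal article. It says controls are randomly selected but not from where, and the sampling frame or a centre adjustment may sit in a fuller document. That stands in part. A reader might infer that controls are drawn at random from all 24 hospitals; the text does not say so, and same-hospital selection may already be the practice. But the matching factors are stated, in two places, and hospital is not one of them. Adding it changes a stated rule and does more than fill in an omitted detail.

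Second, a reader might take the Discussion's phrase "Given the large differences in the HLA gene background" as evidence of regional variation within China. It is not. It follows an account of HPA-1a alloimmunization in Caucasian women and introduces the lack of Chinese data, so it concerns differences between populations.

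Third, ethnicity matching already removes part of any genetic difference, and the two-region model gives no credit for that. This stands: the carriage gaps assumed above must exist within an ethnicity, and the 1.41 needs a four-fold difference in antibody rate plus a three-fold difference in carriage.

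Fourth, sampling error is larger than the bias. At 20% carriage and 98 per group, the standard error of the log odds ratio is √(2·(1/19.6 + 1/78.4)) = 0.36, so a 95% interval spans about a factor of 2 each way. That is true of a single estimate, but a systematic shift still raises the false-positive rate, as the table shows, and six HLA loci are to be examined.

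Fifth, later repair is not impossible. Adjustment could use a few regions in place of 24 centres, and samples may be stored for up to 10 years. This also stands, but it is less precise than matching at selection.

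**Conclusion.** The point holds as a modest, avoidable weakness in the secondary HLA–antibody association. The stated rule permits cross-hospital pairs, and nothing in the stated confounder list or tests deals with centre. Whether bias results is conditional: antibody rate and HLA carriage must both vary by centre within ethnicity, and the document has no data on either. Under the assumed ranges the spurious odds ratio is about 1.05 to 1.4; with equal antibody rates it is 1.00.

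It would go too far to say that centre also undermines the thrombocytopenia comparison. Under the assumptions shown, the shift is at most about 0.75 points against 14.2, and the article specifies EDTA cord blood for all newborn counts. The two primary objectives in Table 1, antibody incidence and NAIT among positive women, are to be described and do not depend on where the controls come from.

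**What to change.** In the Abstract (Methods) and under Recruitment and informed consent, state that each control is selected at random from antibody-negative women of the same hospital, ethnicity and parity. If none exists, use another hospital in the same region. If same-hospital selection is already the practice, say so.

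Under Statistical analysis, keep the pairs in the HLA comparison (McNemar's test or conditional logistic regression), or stratify by centre or region (Mantel–Haenszel). Ignoring the pairing after matching would tend to pull a true odds ratio towards 1.

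The change costs nothing in sample size, ratio or assays. The downside is that a few women with a rare combination of ethnicity and parity, or at a small centre, will need the fallback; the average of 2,312 women per hospital assumes centres of equal size. If hospital proves unrelated to antibody rate, the matching gains nothing and may cost a little precision.
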